**Fig. 1 Fig1:**
[figure not shown]
Flow-chart of participants enrollment and follow up. Note: TB, tuberculosis; MDR-TB, multidrug-resistant tuberculosis

**Table 2 Tab2:** Summary of data collection and timeline

Timeline	Day-0	Day-14	Month-2	Month-5	End of therapy	6th month after treatment
Demographics						
Age, Sex, Occupation	X					
Financial situation	X					
Health conditions						
Comorbidities	X					
Smoking status	X					
Drinking status	X					
Clinical variables						
TB diagnostic information^a^	X					
Physical examination	X	X	X	X	X	X
Renal and liver function tests	X	X	X	X	X	X
Erythrocyte Sedimentation Rata testing	X	X	X	X	X	X
Sputum smear test	X	X	X	X	X	
TB-Score	X	X	X	X	X	
Chest X-ray	X		X	X	X	
Drug susceptibility test	X					
Current medication	X	X	X	X	X	
Drug dose	X	X	X	X	X	
Adverse effect		X	X	X	X	X
Treatment outcome					X	
Biological specimen collection						
Stool sampling	X	X	X	X	X	X
Sputum sampling	X		X	X	X	

^a^*TB* Tuberculosis

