**Methods:**

The study is a multicenter, observational prospective cohort study. Three study sites are purposively selected in the western (Sichuan Province) and eastern (Jiangsu Province and Shanghai) parts of China. Three-hundred patients with bacteriologically confirmed pulmonary TB are enrolled. All eligible patients should be investigated using structured questionnaires before treatment initiation; and be followed up during the treatment at Day-14, Month-2, Month-5, the end of treatment and the sixth month after ending therapy. Stool samples are to be collected at each visit, consisting of six stool samples from each patient. Additionally, 60 healthy volunteers from Sichuan province and Shanghai city will be recruited as healthy controls to form the baseline of patient gut microbiota in the Chinese population. The dynamic changes of gut microbiota in terms of alpha diversity, beta diversity, taxonomic composition are to be illustrated individually from the time at diagnosis until the sixth month after therapy is completed. Furthermore, the diversity and component of gut microbiota will be compared between the groups with and without unfavorable treatment outcome in terms of adverse effect and treatment failure.

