## Background

Tuberculosis (TB), caused by *Mycobacterium tuberculosis* (*M. tb*), has plagued humans for thousands of years and remains a major public health problem. Estimated by the World Health Organization (WHO), there were 10 million TB cases and 1.6 million TB deaths worldwide in 2017 [1]. Among them, 890,000 new TB cases (8.9%) were infected in China, with a mortality rate of 26/100,000 [1]. TB is a curable disease, and the modern TB control program recommends the strategy of directly observed treatment – short-course therapy, which is a six-month standardized treatment using first-line anti-TB drugs (FLDs) including Isoniazid (INH), Rifampicin (RFP), Pyrazinamide (PZA), and Ethambutol (EMB). This potent standardized drug regimen has contributed to an up to 90% cure rate in TB patients during the last three decades. However, the high rate of recurrence and retreatment among TB patients, the ubiquity of severe gastrointestinal adverse reactions [1, 2], and the increasing epidemic of multidrug-resistant tuberculosis (MDR-TB) all suggest that the effectiveness of anti-TB treatment in China has yet to be addressed.

Therefore, introducing new knowledge and clinical strategies to improve the therapeutic effect and clinical prognostics in Chinese TB patients is of great significance. The recent research advances in gut microbiome have shown that these bacteria are not only actively involved in the absorption of food and drugs but also produce bioactive compounds influencing the immune and hormone systems, which is essential to maintain vital functions of the healthy host [3]. Generally, the human gut microbiota shows a large degree of interpersonal diversity [4], and its composition is also affected by many factors such as geography, diet, season, lifestyle, disease state, and in particular, the use of antibiotics [3, 5].

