#### Secondary objectives

To describe the baseline features of gut microbiota before anti-TB treatment among TB patients with different age, gender, health status, disease comorbidity in different regions of China.To compare the characteristics of gut microbiota in terms of diversity and taxonomic composition between TB patients at baseline and healthy controls.To describe the incidence of gut microbiota dysbiosis during anti-TB treatment and its association with adverse effects and unfavorable treatment outcomes in pulmonary TB patients through a case-control study nested in the conducted cohort.To identify the potential microbial markers of unfavorable treatment outcomes.To observe the long-term effect of TB treatment on intestinal microbiota after therapy is completed.

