### Study design

This study is an ongoing multicenter, population-based prospective cohort study conducted in three TB designated hospitals in Eastern and Western China. The study aims to include 300–400 bacteriologically confirmed pulmonary TB patients. Baseline information, including demographics, socioeconomic status, laboratory tests, and disease profiles, as well as sputum and stool samples will be collected from the enrolled patients immediately after TB diagnosis. The patient cohort will be built and followed up during the first-line anti-TB treatment at Day-14, Month-2, Month-5, last day of treatment, and the sixth month after treatment. Information regarding adverse effects, disease progress, and laboratory results will be collected at each visit. Stool samples will be sent to the laboratory for 16S ribosomal ribonucleic acid (rRNA) gene sequencing to identify the alterations in gut microbiota. A comparison of gut microbiota will be performed between newly diagnosed TB patients and healthy controls to reflect the difference in baseline features. After treatment completion, a nested case-control study will be performed between patients with treatment success or failure and patients with or without adverse effects to screen the potential biomarkers from the gut microbiota indicative of therapeutic effect.

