### Study procedures

Patients with bacteriologically-confirmed TB are informed about the study by the study coordinators. After receiving the written informed consent, socio-demographic characteristics (date of birth, gender, education, income, etc.), behaviors (alcohol use, smoking, etc.) and clinical information (concomitant medication, physical examination results, TB severity, etc.) of the participants will be documented by a well-designed structured questionnaire.

According to the national guidelines of TB treatment in China, all drug-susceptible TB patients are recommended hospitalization (2 weeks) for the start of TB treatment. The standardized first-line treatment regimen is comprised of 2 months intensive phase and 4–6 months continuation phase. Considering different treatment stages and national regulations, enrolled TB patients will be sampled at Day-0 (important to sample BEFORE treatment), Day-14, the end of intensive-phase (usually at Month-2), Month-5, the end of the treatment and the sixth month after completion of therapy. During treatment, the disease progresses, adverse effects, TB-scores [24], clinical manifestations, drug regimen, and doses of the patients will be documented. Smear microscopy testing is performed at Day-0, Month-2, Month-5 and the end of therapy. DST testing is carried out at inclusion. Additionally, in total six fecal samples will be collected from the patients at inclusion and each scheduled follow-up visit. Subjects in the healthy control arm will have their fecal specimens collected once at inclusion. Questionnaires will be used to record the socio-demographic and behavioral information as well as the health check-up results.

The bio-specimen will be transported to the TB laboratory at the designated hospitals or local Centers for Disease Prevention and Control within 12 h after collection. Stool samples should be stored at − 80 °C until DNA extraction. Figure 1 and Table 2 provide an overview of the study flow-chart and the timeline of sample and information collection.

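### No medication item is scheduled at the six-month post-therapy visit, so antibiotics taken after treatment go unrecorded and non-recovery of the microbiota could not be securely attributed to TB treatment

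*Protocol article*

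**What the plan says.** The fifth secondary objective is "To observe the long-term effect of TB treatment on intestinal microbiota after therapy is completed". The sample that serves it is the last of six. The abstract's Methods put the final two visits at "the end of treatment and the sixth month after ending therapy".

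Table 2 fixes the items visit by visit. The row "Stool sampling" is marked at all six. The row "Current medication" and the drug-dose row below it are marked at Day-0, Day-14, Month-2, Month-5 and end of therapy, and are blank at the sixth month after treatment. Physical examination, renal and liver tests, erythrocyte sedimentation rate and adverse effects are all marked at that visit.

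Three statements in the text bear on medication:

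- Study procedures, at enrolment: "clinical information (concomitant medication, physical examination results, TB severity, etc.) of the participants will be documented by a well-designed structured questionnaire".
- Study procedures, on treatment: "During treatment, the disease progresses, adverse effects, TB-scores [24], clinical manifestations, drug regimen, and doses of the patients will be documented".
- Study design, at every visit: "Information regarding adverse effects, disease progress, and laboratory results will be collected at each visit".

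The Background lists what shapes the gut microbiota, ending with "lifestyle, disease state, and in particular, the use of antibiotics". Antibiotic intake in the preceding 3 months excludes both patients and healthy controls at entry.

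**The concern.** The protocol itself singles out antibiotics as a determinant of the outcome it measures, and screens for them before the baseline sample and before the control sample. The post-therapy sample comes after six months outside the treatment schedule, and no item records what was taken in that time.

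If diversity or composition has not recovered at six months, there are at least two explanations: a lasting effect of the TB regimen, or a later antibiotic course. Without an exposure record the two cannot be separated. The Microbiome analysis section plans a generalized linear model for change over time that controls for selected confounders, but a variable that was never collected cannot be among them. For patients who have passed the visit, the information could be recovered only from recall or outside records.

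**Working it through.** The point concerns the schedule, and the plan states no figure to reproduce. The check sets the places side by side.

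**Is the blank cell real?** Yes. The stool row has six marks. The adverse-effect row begins with a blank and still ends with a mark in the last column. The medication row has five marks followed by a blank. The columns therefore align, and the omission is not an artefact of how the table was read.

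**Is the visit held?** Yes. Examination, laboratory tests, adverse effects and stool are marked there, so only the medication items are missing.

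**Does the text supply the item elsewhere?**

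| Place | What is recorded | When |
|---|---|---|
| Study procedures, questionnaire | concomitant medication | after consent, at enrolment |
| Study procedures, follow-up | regimen and doses | during treatment |
| Study design | adverse effects, disease progress, laboratory results | each visit |
| Table 2 | medication, dose | Day-0 to end of therapy |

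No place states that medication is recorded after therapy. Smear, sputum and treatment outcome are also unmarked at the sixth month. Relapse might surface under disease progress, but the drugs given for it have no item.

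**How much could it matter?** The documents do not say how many patients take antibiotics in the interval or what effect that has, so the following is only an illustration. Suppose that the true residual dysbiosis equals the 5% that the Sample size section assumes for healthy controls. Suppose also that it is 20% in patients with an unrecorded course. The 20% is borrowed from that section's rate for TB patients and does not measure an antibiotic effect. With a share q exposed:

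observed rate = (1 − q) × 5% + q × 20% = 5% + 15% × q

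| q (assumed) | observed rate | excess (points) |
|---|---|---|
| 5% | 5.75% | 0.75 |
| 10% | 6.5% | 1.5 |
| 20% | 8.0% | 3.0 |
| 30% | 9.5% | 4.5 |
| 40% | 11.0% | 6.0 |

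If only courses in the last 3 of the 6 months matter, and courses are spread evenly, q halves and so does the excess: about 0.4 to 3.0 points. Under these assumptions the error runs toward apparent non-recovery and does not shrink with more patients. Its actual size cannot be derived from the documents.

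**The case against.** Table 2 is offered as an overview, and the questionnaire is not shown. The table is also not exact: it leaves out education, which Study procedures lists, and marks a smear at Day-14 that the text's smear schedule lacks. A blank cell is therefore weaker evidence than a data collection form would be. This lowers certainty, but the table does fix items by visit and the text agrees with it on this one, so the gap is more than condensation.

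The medication row may track only the TB regimen, since it sits directly above the dose row with identical marks. That is plausible, but it does not help: on that reading Table 2 has no row for other antibiotics at any follow-up visit. The objection does show that marking the existing cell would not be enough, because medication on the visit day does not capture six months of history.

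The 3-month antibiotic rule is an enrolment criterion. A reader might infer that the plan breaks its own rule by not applying it to the last sample. The documents do not support that, because the criterion defines who enters. It shows only that the protocol regards recent antibiotics as relevant.

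The objective is the last of five secondary ones and is framed as observation. This stands, and it limits the weight of the point.

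**Conclusion.** The point holds in a limited form. As scheduled, antibiotic exposure between the end of therapy and the six-month sample is not recorded, so non-recovery could not be securely attributed to TB treatment and could not be adjusted for this exposure. This rests on reading Table 2 as the operative schedule. If the unseen questionnaire already takes an interval history, the point reduces to correcting the table.

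Two stronger readings should be resisted. A reader might infer that the sample cannot serve its objective at all. It can: it still describes each patient's microbiota six months after therapy, and only causal attribution is weakened. A reader might also express the bias in standard deviations, for example 10–30% exposed times 0.5–1.0 SD per course, giving 0.05–0.30 SD. Neither input is in the documents, and that product gives full effect to courses more than 3 months old. The size is unknown.

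One secondary objective is affected. The change is still worth making because it is cheap now and hard to make good later.

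**What to change.** At the sixth-month visit, add to Table 2 and the questionnaire an interval history of any antibiotic taken since the end of therapy, including further anti-TB drugs, with name, dates and duration. An item on medication used on the day would not be enough.

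For the fifth secondary objective, keep all patients in the main analysis. Add either an analysis adjusted for intervening antibiotics or a sensitivity analysis excluding patients with intake in the 3 months before that sample. Neither should replace the main analysis, because both condition on an event after treatment. Exclusion in particular could selectively remove patients who were treated again.

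The cost is one or two questions at a visit already held, some recall error, and fewer patients in the restricted analysis. Patients who have already passed the visit would have to be asked retrospectively or checked against outside records.

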### Laboratory methods

#### Smear microscopy testing

Routine smear microscopy testing is carried out at the laboratory of designated TB hospitals using AFB smear microscopy.

#### Drug susceptibility testing

Routine DST is performed according to the Chinese National Guidelines with the proportion method on Lowenstein-Jensen (LJ) medium (sputum culture-positive), and LAPs (sputum culture-negative) according to WHO’s recommendations.

#### Microbial nucleic acid extraction

Microbial genomic DNA will be extracted from the stool samples using the QIAamp DNA Stool Mini Kit (Qiagen, Hilden, Germany). The DNA extraction should be performed in the Class II biologic safety cabinet. The concentration of genomic DNA in each fecal sample will be quantified using a NanoDrop 2000 spectrophotometer (Thermo Scientific, MA, USA). DNA integrity and sizes are assessed using 1% agarose gel electrophoresis.

#### 16S rRNA gene sequencing

Collected fecal samples will be analyzed by 16S rRNA gene sequencing to obtain the information on microbial composition. A nested polymerase chain reaction (PCR) protocol will be employed to amplify and barcode the 16S hypervariable region V3–V4 (primers: 314F: 5′-CCTACGGGRSGCAGCAG-3′ and 806R: 5′-GGACTACVVGGGTATCTAATC-3′) producing ∼425 base pair PCR product. PCR amplification will be performed in 20 μL reactions containing 10× polymerase mix (Life Technologies, Carlsbad, CA, USA), 10 μM of the forward and reverse primers, and 25 ng of template DNA. The PCR program is set as: initial denaturation at 95 °C for 5 min; 25 cycles of denaturation at 95 °C for 30 s, annealing at 56 °C for 30 s, and extension at 72 °C for 40 s; and final extension of 72 °C for 10 min. The dual-indexed amplicon mixture will be pooled according to the manufacturer’s instructions (Illumina, Inc., San Diego, CA, USA), and then sequenced on the Illumina HiSeq 2500 platform to produce 2 × 250 base pair reads.

### Statistical analysis

#### Descriptive data

Appropriate statistical tests will be applied to analyze and present descriptive data. Comparisons between groups will be performed with Student’s *t*-test and Pearson’s Chi-square test for quantitative and categorical variables, respectively.

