### Sample size

Because of the absence of prior data on the study aims of the microbiota in a cohort study design of this topic, a pragmatic approach is chosen to determine the sample size. Based on the previous collaboration with the study sites, each site should enroll 50 eligible TB patients every year so that a patient cohort of 300 cases is expected within 2 years. Referred to the treatment failure rate (10%) in China [1], 30 patients in the conducted cohort are estimated to have unfavorable treatment outcomes. The sample size of microbiota study is usually selected empirically, a wide range of study settings indicates that 30 patients each group would likely be sufficient to assess phenotypic heterogeneity at the molecular level [21, 22].

Healthy controls will be equally recruited from the population taking routine health check-up in Sichuan and Shanghai with a total amount of 60. By assuming the rates of intestinal flora dysbiosis are 20% in TB patients [11] and 5% [23] in healthy controls [23], the sample size of 200 TB patients and 60 healthy controls has over 85% power to detect a significant difference in the composition of gut microbiota at the 5% significance level.

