#### Microbiome analysis

The raw 16S rRNA gene data will be processed to generate amplicon sequence variants (ASVs) using DADA2 program [25]. Taxonomies will be assigned using Silva [26] as the reference database. Alpha diversity (such as Observed ASVs, Chao1, Shannon, Simpson, etc.) and beta diversity measures will be analyzed using QIIME2 [27] and the Wilcoxon and Kruskal–Wallis tests will be used for statistical testing of two and multi-group comparisons, respectively. Principal coordinate analysis will be used to interrogate the robustness of group-wise clustering, and Adonis test will be used to estimate statistical significance of group-wise beta diversity [27]. Generalized linear model (GLM) will be performed to evaluate the influence factors that may affect the gut microbiota of patients, such as gender, body mass index, TB severity, age, morbidities and so on [28]. Then using GLM to estimate the dynamic changes of microbiota composition with the control of selected confounders [29]. Differential abundance analysis of ASVs will be carried out using STAMP [30] and *p*-values will be adjusted for multiple testing (FDR-adjusted Wald Test). Correlations between clinical parameters and bacterial genera will be calculated using canonical correspondence analysis or redundancy analysis [31]. Random forests approach will be performed to find the most important species as marker taxa correlating with unfavorable treatment outcomes. The data will be analyzed using the QIIME2 pipeline and R [32]. A *p*-value or q-value ≤0.05 will be considered as statistically significant.

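### Student's equal-variance t-test is named for descriptive comparisons between groups of clearly unequal size; Welch's version would hold the 5% level if the spreads differ

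*Protocol article*

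**What the plan says.** The Descriptive data paragraph of the Statistical analysis section opens with a general promise: "Appropriate statistical tests will be applied to analyze and present descriptive data". It then becomes specific: "Comparisons between groups will be performed with Student’s" t-test for quantitative variables, with Pearson's chi-square for categorical ones. It does not mention unequal variances or transformation.

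Group sizes come from elsewhere in the article:

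- **Patients vs controls.** The Sample size section states that "the sample size of 200 TB patients and 60 healthy controls has over 85% power".
- **Outcome groups.** The same section expects that "a patient cohort of 300 cases is expected within 2 years" and that "30 patients in the conducted cohort are estimated to have unfavorable treatment outcomes". The Study design section makes this comparison a nested case-control study and gives no ratio of controls to cases.
- **Adverse effects.** The Background cites 20 to 25% of patients with gastrointestinal reactions and liver dysfunction, which is 60 to 75 of 300. The Study design section places this comparison in the same nested study.

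The microbiota measures are analysed by other methods. For alpha and beta diversity, the Wilcoxon and Kruskal–Wallis "tests will be used for statistical testing of two and multi-group comparisons, respectively".

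**The concern.** Student's test estimates one common variance, and the larger group dominates that estimate. With equal group sizes this does little harm. With unequal sizes the standard error is wrong whenever the spreads differ. If the smaller group is the more variable, the standard error is too small and differences are declared too often. If the larger group is the more variable, the standard error is too large and real differences are missed.

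Table 2 schedules renal and liver function tests and the erythrocyte sedimentation rate for patients. Controls contribute health check-up results. Equal spread in sick and healthy people cannot be presumed for measurements of this kind. At stake is which patient characteristics are reported as differing between groups, alongside the microbiota results.

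**Working it through.** **The plan's own figure.** The article states no error rate for the t-test beyond the 5% level. Its only power figure concerns proportions, 20% vs 5% at 200 vs 60, and it reproduces:

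- pooled proportion (40 + 3)/260 = 0.1654
- null standard error √(0.1654 × 0.8346 × (1/200 + 1/60)) = 0.0547
- alternative standard error √(0.16/200 + 0.0475/60) = 0.0399
- power Φ((0.15 − 1.96 × 0.0547)/0.0399) = Φ(1.07) = 85.8%

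So the 200 vs 60 sizes can be taken as planned.

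**Inputs for the check.** Sizes 60 and 200 are from the Sample size section. The level is 0.05, taken as two-sided because the article does not say. The SD ratios are assumed.

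**Formula.** Let the smaller group have size n1 and SD s1, and the larger n2 and s2. The variance Student's test uses is, on average,

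E = [((n1 − 1)s1² + (n2 − 1)s2²)/(n1 + n2 − 2)] × (1/n1 + 1/n2).

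The true variance of the difference is T = s1²/n1 + s2²/n2. In large samples the true level is 2 × [1 − Φ(1.96 × √(E/T))].

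**60 controls vs 200 patients.**

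- *Patients' SD twice as large* (s1 = 1, s2 = 2): E = (59 + 796)/258 × 0.021667 = 0.07180; T = 1/60 + 4/200 = 0.03667; E/T = 1.958; level 0.6%.
- *Patients' SD 1.5 times as large*: E = (59 + 447.75)/258 × 0.021667 = 0.04256; T = 0.02792; E/T = 1.524; level 1.6%.
- *Equal SDs*: E/T = 1; level 5.0%.
- *Controls' SD 1.5 times as large*: E = (132.75 + 199)/258 × 0.021667 = 0.02786; T = 0.04250; E/T = 0.656; level 11.3%.
- *Controls' SD twice as large*: E = (236 + 199)/258 × 0.021667 = 0.03653; T = 0.07167; E/T = 0.510; level 16.2%.

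Simulation with normal data (400,000 datasets per setting) gives 0.6%, 1.6%, 5.0%, 11.3% and 16.2%. On the same data, Welch's test stays between 4.97% and 5.09%.

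**75 vs 225 (25% of 300 with adverse reactions, all others as comparison).** By the same formula, the level is 10.7% or 15.1% if the smaller group's SD is 1.5 or 2 times larger, and 0.8% if the larger group's SD is twice as large.

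**Outcome groups.** The effect depends on the unstated control ratio.

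- *30 vs 30*: E = T at any SD ratio, so the level is about 5%.
- *30 vs 60*: 1.6% if the cases' SD is half the controls', 11.1% if it is twice.
- *30 vs 270* (everyone else used as controls; 300 − 30 = 270): 0.1% and 24.7% for the same two ratios.

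**Skewed data.** With identical lognormal distributions in both groups (log-SD 1), Student's test gives 4.6 to 4.8%. Welch's gives 6.1% at 60 vs 200 and 9.4% at 30 vs 270. On the log scale such data are normal, and Welch's test then holds its level.

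**Power cost of Welch when variances are equal** (4,000 datasets): 79.6% to 79.2% at 60 vs 200; 79.7% to 77.9% at 30 vs 270.

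**The case against.** Four objections deserve an answer.

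**The named test governs little.** It sits under descriptive data, after a promise of appropriate tests. Diversity, composition, confounder adjustment, differential abundance and marker selection all use other methods. This stands, and it is why the point is minor.

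**The variance form is a detail for the full plan.** This stands in part. An article may leave such detail out, but this one names the test, and Student's test ordinarily means the equal-variance form. If the full plan already specifies unequal variances, only the wording needs aligning.

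**Inflation in the patient-control comparison needs healthy controls to be the more variable group.** That is fair. If illness increases spread, the likelier fault there is a conservative test that misses differences, the 0.6% to 1.6% side. Neither direction can be settled from the article.

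**Welch's test is not a free correction.** This also stands. If skewed variables are left untransformed, it is too liberal even when the distributions are identical, and Student's is not.

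A reader might also infer that the Wilcoxon test for diversity has the same defect and should be replaced by the Brunner–Munzel test. The article does not support that. Wilcoxon is valid for its usual null hypothesis of identical distributions. Brunner–Munzel tests a different hypothesis, so the choice is one of preference.

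**Conclusion.** The point holds as a minor improvement. Student's t-test is named, and the printed 200 vs 60 comparison is unequal enough for its level to depend on the SD ratio. With normal data the level runs from about 0.6% (patients' SD twice the controls') to about 16% (controls' SD twice the patients'), and it is 5% if the SDs are equal. The ratios are assumptions.

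A reader might infer an error rate anywhere from 0.1% to 36% across the planned comparisons. The documents do not support that. Both ends belong to 30 vs 270 only, a split the article never states. They also use different assumed ratios: half the SD for 0.1% and three times the SD for 36%. The outcome and adverse-effect comparisons are affected only if the nested study uses unequal groups. The microbiota analyses and the primary objective are unaffected.

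**What to change.** In the Descriptive data paragraph, replace Student's t-test by Welch's t-test for quantitative variables, and state that clearly skewed laboratory variables will be analysed on the log scale. The Wilcoxon test under Microbiome analysis can stay.

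The change is one sentence, uses standard R functions and needs no new data. If variances are equal, it costs about 0.4 percentage points of power at 60 vs 200 (79.6 − 79.2) and about 1.8 at 30 vs 270 (79.7 − 77.9). If the log transformation is omitted for skewed variables, some inflation remains, mild at 60 vs 200 and larger at 30 vs 270. Log-scale results compare geometric rather than arithmetic means and should be labelled so.
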